#### Sample size {14}

This is a phase 1b/2a study aiming to evaluate the effect of nebulised unfractionated heparin on procoagulant markers and the safety of nebulised heparin in patients receiving advanced respiratory support for COVID-19 lung disease. This has not been studied previously, and as such, data does not exist to power the study accurately to assess clinical outcomes. We have chosen to base our power analysis on some of our own in house data for d-dimer levels in COVID patients who required ICU care (12 patients) and those who did not (26 patients) (unpublished data from very early in the pandemic).

Based on an estimation that nebulised heparin may reduce the d-dimer levels in ICU patients (mean = 944.8ng/ml [SD = 485.3]) to those experienced in ward patients (mean = 436.5ng/ml [SD = 604.0]), with an alpha level of 0.05 and a power of 90% to detect a type II error, 19 patients per group would be required. Increasing the number by 1 per group to allow for potential dropout gives a sample size of 20 patients per arm of the study, with a total of 40 patients to be enrolled. The safety profile of administering nebulised heparin to invasively ventilated patients with COVID-19 will be a co-primary outcome. The study is not powered for analysis of the co-primary endpoint of serious adverse events due to insufficient pre-existing data in this population. Power analysis is based only on the outcome of d-dimer as described above.

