### Statistical methods

#### Statistical methods for primary and secondary outcomes {20a}

Demographic and baseline characteristics of the study population will be summarised using appropriate graphical and numerical summaries for each treatment group and by site. The primary analysis approach will be an intention-to-treat analysis, with a per-protocol analysis also being carried out. The per-protocol analysis will include any patient who received any dose of the study drug in the treatment group and any patient who underwent data collection for at least one time point in the standard care group. A safety analysis set will be included including all recruited patients. For effectiveness analysis, we will use the 2-sample *t*-tests (or suitable non-parametric test depending on data distribution) for the between-group difference in d-dimer levels and generalised linear (or non-linear as appropriate) mixed effects models for the analysis of longitudinal data, using appropriate link functions depending on the type of outcome variable. This analysis will be used to compare the treatment effect, while adjusting for patient characteristics (e.g. Horowitz index of lung function (P/F ratio), Sequential Organ Failure Assessment (SOFA) score, body mass index (BMI), sex and age) as appropriate for all primary and secondary efficacy outcomes. A Cox proportional hazards model will be used to model time to event responses. Generalised linear models will be used for the analysis of safety outcomes. Primary and secondary outcome data will be suitable for meta-analysis to further assess clinically relevant outcomes. Interval estimates (95% confidence intervals) for the treatment effect will be reported accordingly.

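### The protocol's own means and SDs do not give 90% power at 19 per group: a two-sided 5% t-test has about 79% (82% at 20), and power for the d-dimer AUC is not given

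*Protocol article*

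**What the plan says.** The section Sample size {14} bases power on in-house d-dimer data from "COVID patients who required ICU care (12 patients) and those who did not (26 patients"). The assumed effect is that heparin brings d-dimer down from the level in "ICU patients (mean = 944.8ng/ml [SD = 485.3") to the level in "ward patients (mean = 436.5ng/ml [SD = 604.0"). It then concludes: "with an alpha level of 0.05 and a power of 90% to detect a type II error, 19 patients per group would be required". The step to 20 per arm and 40 in total is described as "Increasing the number by 1 per group to allow for potential dropout". The section adds that d-dimer is the only outcome on which power rests, so this is the trial's sole power figure.

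The section does not say whether the test is one-sided or two-sided, or how the two SDs were combined. Statistical methods {20a} plans a two-sample t-test (or a non-parametric alternative) for d-dimer, mixed models for longitudinal data, and: "Interval estimates (95% confidence intervals) for the treatment effect will be reported accordingly".

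Outcomes {12} defines the d-dimer co-primary as a difference over time, measured by the area under the curve on days 1, 3, 5 and 10.

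**The concern.** A difference of 508.3 ng/ml against SDs of 485.3 and 604.0 is a standardised effect a little above 0.9. A two-sided 5% comparison at that effect size normally needs about 25 per group for 90% power, so 19 looks too few. If so, the protocol claims a smaller risk of missing the assumed effect than its design carries, and a non-significant d-dimer result could be given more weight than it deserves.

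Two further points sit in the same sentences. The calculation concerns a d-dimer level while the outcome is an AUC. And the phrase "a power of 90% to detect a type II error" misdescribes power, which is one minus the type II error rate.

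**Working it through.** **Inputs, all from Sample size {14} unless noted**
- Means 944.8 and 436.5, so the difference is 944.8 − 436.5 = 508.3 ng/ml.
- SDs 485.3 and 604.0.
- Alpha 0.05, sidedness not stated; stated power 90%; 1:1 allocation (Sequence generation {16a}).
- Two-sample t-test (Statistical methods {20a}).

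**Standardised effect with both SDs**
- Root-mean-square SD = √[(485.3² + 604.0²)/2] = √[(235,516 + 364,816)/2] = 547.9.
- Effect = 508.3/547.9 = 0.928.

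**Trying to reproduce 19 per group**

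Normal approximation: n per group = 2(z_alpha + z_power)²/effect². The last two columns use the noncentral t distribution with 2n − 2 degrees of freedom and noncentrality effect × √(n/2).

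| Reading | n for 90%, normal approximation | n for 90%, t-test | t-test power at 19 | t-test power at 20 |
|---|---|---|---|---|
| Two-sided, both SDs | 2(1.960 + 1.282)²/0.928² = 24.4, so 25 | 26 | 79.5% | 81.6% |
| One-sided, both SDs | 2(1.645 + 1.282)²/0.928² = 19.9, so 20 | 21 | 87.7% | 89.2% |
| Two-sided, ICU SD in both arms (effect 508.3/485.3 = 1.047) | 19.2, so 20 | 21 | 88.1% | 89.7% |
| One-sided, ICU SD in both arms | 15.6, so 16 | 17 | 93.6% | 94.6% |
| Two-sided, SDs pooled by 12 and 26 patients (570.4; effect 0.891) | 27 | 28 | 76.2% | 78.4% |

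The second and third readings come close to 19, but only if 19.9 or 19.2 is rounded down. For comparison, 80% power, two-sided, with both SDs gives 2(1.960 + 0.842)²/0.928² = 18.2, which rounds up to 19. The document does not show which route was taken.

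**Checks on the two-sided, both-SD result**
- Welch t-test: 79.4% at 19 and 81.5% at 20.
- Simulation, 200,000 runs, pooled-variance t-test with unequal SDs: 79.5% and 81.8%.
- Normal approximation: 81.6% and 83.5%.

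**Level versus AUC**

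The documents give no SD or correlation for the AUC, so this part is illustrative. Assume the SD is 547.9 at every visit, one common within-patient correlation, and a trapezoid time average over days 1, 3, 5 and 10. The weights are 1, 2, 3.5 and 2.5 out of 9. Take 20 per arm and a two-sided 5% t-test. Suppose the first sample carries no effect and the full 508.3 is present from day 3, so 8/9 of the difference remains in the average.

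| Within-patient correlation | Power for the time average |
|---|---|
| 0.3 | 94.8% |
| 0.5 | 88.6% |
| 0.7 | 81.7% |
| 0.9 | 75.1% |
| 1.0 (no gain from averaging) | 72.0% |

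The single-level figure of 81.6% lies inside this range. Averaging lowers the variance and can outweigh the lost effect, so the mismatch has no fixed direction.

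**The case against.** The strongest reply is that the protocol states neither sidedness nor how the SDs were combined. A one-sided 5% test with both SDs gives 89.2% at the enrolled 20, and a two-sided test with the ICU SD alone gives 89.7%. Both are close to 90%, so calling the figure plainly wrong assumes a two-sided test and use of both SDs.

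Part of this stands: the shortfall to 79–82% is conditional on a two-sided test and must be reported so. It does not rescue the sentence as written, which claims 90% at 19, not 20. A one-sided test with both SDs needs 20 to 21, and the ICU-only route discards an SD that the same sentence offers as an input. Combining both departures exceeds 90% at 19, but that calculation would have asked for 16 or 17, not 19.

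It can also be said that this is a small proof-of-principle study that will report intervals. That limits how far a null result can be misread. It does not make the power figure correct.

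A reader might go further and infer that the AUC outcome dilutes the effect, so that true power is lower still. The documents do not support that. Outcomes {12} puts the first sample on day 1 and Participant timeline {13} puts it on day 0. Dosing runs from enrolment, so whether the first value is free of treatment effect is not settled. No effect time course or correlation is given, and modest correlations raise power. That the in-house data are one value per patient is likely but is not stated.

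**Conclusion.** The stated 90% power at 19 per group does not follow from the protocol's own inputs. With both SDs and a two-sided 5% t-test, power is about 79% at 19 and 82% at 20. The type II error is therefore about 18–21%, roughly double the stated 10%, and 90% would need 26 per group (25 by normal approximation).

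This rests on one assumption, the two-sided test, which is the natural reading of an unqualified 0.05 with 95% intervals. With both SDs and a one-sided test the shortfall is small (87.7% at 19, 89.2% at 20) but remains.

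For the AUC co-primary, the power is simply not given. It may be above or below the single-level figure.

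**What to change.** Keep 40 patients and restate the figure, for example: *20 per arm gives about 82% power (two-sided alpha 0.05, two-sample t-test) for a 508 ng/ml difference in d-dimer level with SDs 485.3 and 604.0; 19 evaluable per arm gives about 79%.*

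In the same paragraph:
- State the sidedness and how the two SDs are combined.
- Say that the figure applies to a d-dimer level and not to the AUC, or add AUC power under stated assumptions on effect timing and within-patient correlation.
- Replace the phrase about detecting a type II error with a plain pairing of power and type II error, using the corrected figures (about 82% and 18% at 20 per arm).

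The cost is wording only. No patients are added; the price is a less favourable stated power.

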### Recruitment {15}

Recruitment will be organised and supervised by intensive care research and clinical research facilities within recruiting centres and in line with national and international standards and guidelines, and local standard operating procedures. The research nurses/coordinators and investigators at each site will work with clinicians to identify potential candidates for enrolment. A screening log will be maintained of patients who met the inclusion criteria but were not enrolled, with the reason for exclusion recorded on the log. If a patient is deemed eligible, the patient’s next of kin will be contacted, and a patient information leaflet will be sent to them or given to them in person if possible.

### Assignment of interventions: allocation

#### Sequence generation {16a}

Allocation will be carried out after consent is confirmed, via a central, secure web randomisation process hosted by the contract research organisation (CRO). Allocation will be in a one-to-one ratio, with variable block size randomisation. The code for the randomisation process is embedded in the eCRF. The Programme R was used to generate the randomisation sequence.

#### Concealment mechanism {16b}

Blocks of variable size and a random seed will be used to ensure allocation concealment cannot be violated by deciphering the sequence near the end of each block. To further protect from deciphering, block size will not be revealed to site investigators. Site-level randomisation will be used. At randomisation, each participant is assigned to nebulised heparin or standard care. There is a one-to-one allocation ratio.

#### Implementation {16c}

Research nurses and investigators at each site will work with clinicians to identify potential candidates for enrolment. The randomisation process is embedded in the eCRF, and once the patient’s screening data has been inputted and they are eligible, the investigator will request randomisation via the eCRF.

### Assignment of interventions: blinding

#### Who will be blinded {17a}

This is an open-label trial, and therefore, all patients facing study personnel will be unblinded. However, the statistician performing data analysis will be blinded to allocation.

#### Procedure for unblinding if needed {17b}

Not applicable—this is an open-label trial.

### Data collection and management

#### Plans for assessment and collection of outcomes {18a}

Data will be collected by trained staff at each site under the supervision of the principal investigator using a case report form and data dictionary developed by the management committee (Attachment CRF). Baseline data will be gathered from health records at the treating institution. It may also be necessary in a small number of cases to obtain information from other healthcare providers. Daily data for days 0 to 10 while in intensive care: Data are gathered from health records at the treating institution for each day that the patient is in ICU up to and including day 10. Day 28 and day 60 data are gathered from health records at the treating institution and, where necessary, other healthcare providers. Adverse event or adverse reaction data are gathered from health records at the recruiting institution and, where necessary, other healthcare providers and the patient or proxy.

The study will be conducted in accordance with the current approved protocol, International Conference on Harmonisation (ICH) Good Clinical Practice (GCP), relevant regulations and standard operating procedures. All effort shall be taken to ensure that data collected is accurate, complete and reliable. The site must facilitate all required monitoring and respond to queries in a timely manner. All data will be reviewed for completeness and logical consistency by the data management team. Data queries will be generated via the electronic data capture system to correct or clarify data or request missing information. The designated site staff will be required to respond to these queries in accordance with data entry and data query timelines for the study.

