#### Outcomes {12}

The co-primary outcomes are:A between-group difference in d-dimer levels over time, assessed by measurement of area under the curve (AUC) on days 1, 3, 5 and 10A between-group difference in the occurrence of serious adverse events (SAEs) as listed in the safety analysis

Secondary efficacy outcomes include analysis of between-group differences in:Oxygenation index (OI) = (FiO_2_ × M_PAW_)/PaO_2_ will be recorded every 6 hPulmonary compliance will be recorded every 6 h up to day 10 in invasively ventilated patientsDynamic pulmonary compliance is measured automatically on our ventilators (Puritan Bennett and Servo I) and recorded on the ICU Clinical Information System), measured as ∆V/∆PInflammatory and coagulation markersIL-1β, IL-6, IL-8, IL-10, soluble tumour necrosis factor receptor 1, C-reactive protein, procalcitonin, ferritin, fibrinogen and lactate dehydrogenase LDH will be assessedAUC measurement for these inflammatory and coagulation markers on days 1, 3, 5 and 10Ratio of IL-1β/IL-10 and IL-6/IL-10Time to separation from invasive ventilation to day 28, where non-survivors to day 28 are treated as though not separated from invasive ventilation, measured in daysNumber tracheotomised to day 28 (*N*)Time to separation from the ICU to day 28, where non-survivors to day 28 are treated as though not separated from invasive care measured in daysSurvival to day 28, survival to day 60 and survival to hospital discharge, censored at day 60

Additional outcomes include:Time to separation from invasive ventilation to day 28, among survivorsNumber treated with neuromuscular blockers instituted after enrolment to day 10Any administration of neuromuscular blocking drugs will be recordedNumber treated with prone positioning instituted after enrolment to day 10Number treated with extra-corporeal membrane oxygenation instituted after enrolment to day 10Time to separation from the ICU to day 28, among survivors, measured in daysNumber residing at home or in a community setting at day 60Number residing at home or in a community setting at day 60, among survivors

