Safety outcomes include analysis of between-group differences in:Air quality samples from an infection control perspective (A TSI optical particle sizer device will be used to collect data on fugitive aerosol emissions during nebulisation, and throughout randomly selected 24-h periods in intubated and non-intubated patients, and in control and treatment arm patients.) This will be a descriptive analysis of air quality information in a selected number of patients.Number of patients transfused red blood cells to day 10Volume of red blood cells transfused to day 10Number who record major bleeding to day 10‘Major bleeding’ is defined as bleeding that results in death and/or bleeding that is symptomatic and occurs in a critical area or organ (intra-cranial, intra-spinal, intra-ocular, retroperitoneal, intra-articular or intramuscular with compartment syndrome) and/or bleeding that results in a fall in haemoglobin of 20g/l or more, or results in transfusion of two or more units of whole blood or red cells [13]Number of patients who record clinically relevant non-major bleeding as defined by the International Society on Thrombosis and Haemostasis [14]Number who record a diagnosis of heparin-induced thrombocytopenia (HIT)Number who record other adverse events and reactionsAdverse events will be assessed systematically with patient and chart reviews on a daily basis, with all clinical events reviewed and assessed by the investigator, and adverse events recorded and reported appropriately. AEs will be classified by organ system

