-Treatment with unfractionated heparin, intravenously or subcutaneously; LMWH, intravenously or subcutaneously; lopinavir-ritonavir; remdesivir; hydroxychloroquine; interferon-β; interleukin antagonists; oseltamivir, laninamivir, zaninamivir or peramivir; macrolide; non-macrolide antibacterial; antifungal; corticosteroid; inotrope or vasopressor infusion; renal replacement therapy; neuromuscular blocker; prone positioning; and extra-corporeal membrane oxygenation

- Volume of packed red cells and whole blood transfused

- Highest APTT

- Blood samples will be collected for inflammatory marker and coagulation parameter assessment as per the primary and secondary outcomes, on days 0, 3, 5 and 10

*Day 28*: The following data are gathered from health records at the treating institution and, where necessary, other healthcare providers:

- Date of first diagnosis of COVID-19 (clinical diagnosis)

- Date of first positive respiratory sample for SARS-CoV-2 and the sample type

- Acute hospital discharge status at day 28 and, if discharged, the date of discharge and discharge destination including deceased

- Readmission to ICU during the acute hospital admission and prior to day 28

- ICU status at day 28 and, if not in the ICU at the end of day 28, the final date and time of ICU discharge

- Invasive ventilation status at day 28 and, if not receiving invasive ventilation at the end of day 28, the final date and time that invasive ventilation was stopped

- Tracheotomy and, if performed, the procedure date

*Day 60*: The following data are gathered from health records at the recruiting institution and, where necessary, other healthcare providers and the patient or proxy:

- Vital status at day 60 and, if deceased, the date of death and whether death related (directly or indirectly) to COVID-19 infection

- Place of residence at day 60

- If not discharged from the acute hospital discharge status by day 28, the acute hospital discharge status at day 60 is ascertained and, if now discharged, the date of discharge and the discharge destination including whether deceased.

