#### Plans to promote participant retention and complete follow-up {18b}

N/A — participation by patient is only required while in ICU. Follow-up requires using healthcare records and information from primary care providers only. This is an intention-to-treat study design.

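### Transfusion outcomes run to day 10 for all patients, but the daily-data rule covers ICU days only; the sections conflict and ward transfusions may go uncounted

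*Protocol article*

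**What the plan says.** **Outcome.** The safety list in Protocol article, Outcomes {12}, contains the number of patients given red cells and the volume given, each to day 10 and each as a between-group comparison. Neither is restricted to time in ICU. Statistical methods {20a} sets the population: "A safety analysis set will be included including all recruited patients".

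**Collection, first statement.** Participant timeline {13} lists, among the items taken from health records for days 0 to 10, "Volume of packed red cells and whole blood transfused". It attaches no ICU condition.

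**Collection, second statement.** Plans for assessment and collection of outcomes {18a} introduces the same period as "Daily data for days 0 to 10 while in intensive care" and says the data are gathered "for each day that the patient is in ICU up to and including day 10". The retention section {18b} adds that "participation by patient is only required while in ICU", although it also foresees follow-up through healthcare records.

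**Later collection points.** The day 28 and day 60 lists in {13} cover discharge, ICU and ventilation status, tracheotomy, vital status and residence. Neither includes transfusion.

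**Separate route for events.** Section {18a} also says: "Adverse event or adverse reaction data are gathered from health records at the recruiting institution", with other providers and the patient or proxy as further sources. That sentence carries no ICU limit.

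**The concern.** An outcome with a fixed window needs a collection rule that covers the window. Here the outcome ends at day 10 for everyone, while under {18a} the daily data end at ICU discharge. A patient who leaves ICU on day 4 and is given one unit on the ward on day 7 belongs in both transfusion outcomes, but {18a} would not pick that unit up.

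The gap matters more for transfusion than for the other items limited to day 10. Neuromuscular blockade, prone positioning and ECMO are essentially ICU treatments, so an ICU limit costs them little. Red cells are also given on wards. Patients on high-flow nasal oxygen are eligible, so leaving ICU before day 10 is plausible.

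The loss need not be equal between arms. The rationale is that heparin hastens recovery, and "Time to separation from the ICU to day 28" is itself an efficacy outcome. If one arm leaves ICU alive sooner, it has fewer days on which a transfusion can be recorded and looks better on transfusion for that reason alone. In an open-label trial of an anticoagulant, transfusion is one of the more objective harm measures and worth protecting.

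**Working it through.** The article states no transfusion rate, no ICU stay and no power for this outcome, so there is no figure of the plan to reproduce. The check has two parts.

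**1. The sections side by side**

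| Section | Window | ICU limit? |
|---|---|---|
| Outcomes {12}: number and volume transfused | to day 10 | no |
| Participant timeline {13}: transfused volume | days 0 to 10 | no |
| Collection of outcomes {18a}: daily data | to day 10 | yes, stated twice |
| Timeline {13}: day 28 and day 60 lists | – | no transfusion item |

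Section {13} read alone gives full capture. Section {18a} read alone does not, and no later collection point repairs it. The two describe the same data and cannot both be the rule.

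**2. Size if {18a} governs (all rates assumed)**

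*Volume.* Take a 10-day window. Let f be the share leaving ICU alive by day 10, on day 6 on average, so that each leaver has 4 unobserved days. Let r be the ward hazard divided by the ICU hazard, the same in both arms. Deaths are left out, because death ends the risk period.

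- Recorded exposure: 10 − 4f.
- True exposure in ICU-day equivalents: 10 − 4f + 4fr.
- Share captured: (10 − 4f)/(10 − 4f + 4fr).
- Artefactual ratio: share captured in the faster arm divided by share captured in the slower arm.

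| Leaving ICU, faster v slower arm | r = 1 | r = 0.5 | r = 0 |
|---|---|---|---|
| 60% v 40% | (7.6/10)/(8.4/10) = 0.90 | (7.6/8.8)/(8.4/9.2) = 0.864/0.913 = 0.95 | 1.0 |
| 70% v 30% | (7.2/10)/(8.8/10) = 0.82 | (7.2/8.6)/(8.8/9.4) = 0.837/0.936 = 0.89 | 1.0 |

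The share of transfused volume missed in an arm is 4fr/(10 − 4f + 4fr). For f = 0.2, 0.4 and 0.6 this is 8%, 16% and 24% at r = 1, and 4%, 9% and 14% at r = 0.5.

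*Number of patients transfused.* With daily ICU probability h and L ICU days, the recorded risk is 1 − (1 − h)^L. Take h = 0.03, with 10 ICU days in one arm and 7 in the other:

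- Slower arm: 1 − 0.97^10 = 26.3%, or 5.3 of 20 patients.
- Faster arm: 1 − 0.97^7 = 19.2%, or 3.8 of 20.
- At equal ward and ICU hazard the true risk is 26.3% in both arms, so the false difference is −7.1 points.
- At half the ward hazard the artefact is −3.6 points, at a quarter −1.8, and at zero it vanishes.
- For h from 0.01 to 0.05 at equal hazard, the false difference with 7 ICU days runs from −2.8 to −10.0 points.

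For scale, the standard error of the recorded difference with 20 per arm is √(0.263×0.737/20 + 0.192×0.808/20) = √(0.00969 + 0.00776) = 0.132, or about 13 points.

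**After the fix**, every patient is observed to day 10 or death, the captured share is 1 in both arms, and the artefact is zero under any of these assumptions.

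**The case against.** **The timeline already allows full capture.** This stands, and it changes the nature of the point. Section {13} has no ICU limit and {18b} foresees use of healthcare records. A reader of {18a} might infer that under-collection is settled; the article supports only a conflict between its sections.

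**Ward days need not be scored as zero.** This also stands. A reader might infer that a discharged patient is recorded as not transfused, volume 0. No section says how uncollected days are coded. They could be treated as missing, and the case report form and data dictionary that might settle this are not shown. Treating them as missing would still put an assumption in place of a fact available in the chart.

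**Bleeding has another route.** This stands in part. The major-bleeding definition includes bleeding that "results in transfusion of two or more units of whole blood or red cells", or a haemoglobin fall of 20 g/l or more. Clinically relevant non-major bleeding is a further outcome, and serious events are reported to 90 days after the last dose. It would be wrong to say that ward transfusion has no route at all. The route is partial, however: Procedures for recording adverse events {22} narrows routine recording of non-serious events to those considered related, up to 96 h after the last dose. A single ward unit not reported as such an event has no stated path into the two transfusion outcomes.

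**Ward days are largely off treatment.** Table 2 has nebulised heparin withheld outside the higher-level care setting, so less of the drug-safety signal is at stake. The outcomes as defined still run to day 10.

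**Deaths could offset the bias.** This does not stand. Early death shortens ICU time, but it also ends the risk period and hides no transfusion.

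**The distortion is inside sampling noise.** True with 20 per arm, and {14} says the trial is not powered for serious adverse events. But a confidence interval shows sampling noise and does not show a collection gap.

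**Conclusion.** The point holds as a conflict with a conditional consequence. The outcome definition and the timeline imply capture to day 10 for everyone; the collection section limits the daily data to ICU days. If the collection section governs, ward transfusions outside the adverse-event route are lost, and the comparison tends to favour the arm that leaves ICU alive sooner.

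A reader might go further and infer a demonstrated bias in favour of heparin. The documents do not support that. They do not say that ICU stay will differ, or in which direction, and they give no rate from which a size could be derived. The volume ratios of 0.90 and 0.82 need equal ward and ICU hazards as well as the assumed exit shares; at half the ward hazard they are 0.95 and 0.89, and with no ward transfusion 1.0. The 70% v 30% split is itself a very large assumed difference. This is a modest defect in safety outcomes outside the co-primary pair. It deserves correction because analysis cannot recover data that were never gathered, and the remedy is cheap.

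**What to change.** Reconcile {12}, {13} and {18a} by adding to {18a} that red-cell transfusion (yes/no and volume) is collected from the hospital record to day 10 or death for every randomised patient, regardless of location. The timeline entry in {13} can then stand, with the same words added for clarity.

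The cost is a few ward days of chart review for each patient discharged from ICU before day 10, in a trial of 40, with no new test or visit.

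The alternative is to redefine both outcomes as transfusion during the ICU stay and report them with days at risk. That would make the sections consistent without extra work, but it ties a safety comparison to a length of stay that treatment may affect, so it is second best.
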